### Sleep questionnaires

The Pittsburgh Sleep Quality Index (PSQI), which measures quality and patterns of sleep during the past month, will be completed at baseline and at the one-month follow-up. The PROMIS – Sleep Disturbance and the PROMIS – Sleep Related Impairment questionnaires will be completed weekly from baseline until the day of surgery, preoperatively within 24 h of surgery and weekly after surgery through the one-month follow-up. These questionnaires may be completed in person or via telephone.

### Blood collection

Blood will be collected to investigate whether the use of a meditation regimen results in a favorable modulation of inflammatory and stress biomarkers secondary to surgery. Collection will occur at baseline, preoperatively (within 24 h before surgery), and on postoperative day 2 for all participants. At each time, approximately 10 cc will be collected. All specimens will be centrifuged, plasma will be aliquoted into smaller cryovials, and frozen at − 80 °C for future use. These specimens will be stored in a biorepository which will be later used to analyze the markers of inflammation.

### Postoperative pain assessment

Postoperative pain will be assessed with a standard 11-point scale and by pain medication requirements. Pain scores will be obtained during the entire hospital stay by asking the individual and collected from the medical record when documented clinically. Pain medication intake in the first 48 h postoperatively will be ascertained from the medical record.

### Satisfaction survey

At the time of the one-month follow-up assessment, or if a participant withdraws from the study, the individuals will be asked to complete a brief satisfaction survey. This survey asks about the patients’ perception of their thinking, memory, attention, and overall wellbeing. If participants were randomized to the control group, they will be asked whether they would be interested in a meditation regime. Participants randomized to either meditation group will be asked about their experience completing the meditation practices, as well as any other feedback related to the study intervention, which will be considered during design of a future study.

### Adverse event monitoring

Since the study participants are undergoing high-risk surgery, it is expected that they may have several adverse health events during their hospital course unrelated to the study intervention. Further, the study intervention is non-invasive and carries minimal risk; therefore, we will limit the scope of our adverse event (AE) reporting to all serious AEs related to study procedures or unexpected non-serious AEs believed to be related to the study procedures. An AE includes changes in the patient’s stress and anxiety; therefore, we will monitor and report abnormal changes in the DASS-21. If the score from any of the three categories (depression, anxiety, stress) falls into the “Severe” or “Extremely Severe” range, the participant will be dropped out of the study for further clinical evaluation and management.

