### Neurocognitive and psychological assessments

A trained research team member who remains blinded to treatment allocation will perform baseline cognitive, delirium, anxiety, and depression assessments. Cognitive function will be assessed using the Montreal Cognitive Assessment (MoCA), supplemented with days of the week (DOW) and months of the year (MOY) for additional attention testing. The Delirium Symptom Interview (DSI) will be used to capture delirium. The Depression, Anxiety, and Stress scale (DASS-21) will be used to assess the baseline psychological state. Using data from the cognitive testing and DSI, the researcher will complete the Confusion Assessment Method (CAM), which includes an assessment of delirium using the CAM diagnostic algorithm. If this baseline assessment shows a DASS-21 depression score > 10 or MoCA score < 10, the individual will be excluded from the study.

To assess the changes over time, or the possible effect of perioperative meditation, a telephonic MoCA (t-MOCA) will be administered preoperatively within 24 h before surgery. These assessments will take place before initiation of any sedatives or other medications that may affect the patient’s performance or ability to complete the assessment.

On each postoperative day during the hospital stay, a blinded research team member will administer a standard cognitive assessment, including DOW, MOY, CAM, and the DSI. If an individual is intubated postoperatively, a CAM-ICU will be performed instead of a CAM assessment. If daily assessments have plateaued for three consecutive days and the patient remains CAM-negative each day, assessments will then be completed every other day if the individual remains CAM-negative, until the date of discharge. On the day of discharge, the MoCA, DOW, MOY, CAM, DSI, and the DASS-21 will be completed.

A follow-up assessment will be administered at one month (± seven days) after the date of surgery. These will be completed by a blinded research team member via telephone and will include a T-MoCA, DOW, MOY, CAM, DSI, and DASS-21. Medications that were taken 6 h before the assessments, as reported per the individual, will be documented at all time points.

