### Statistical analysis

In this feasibility study, a convenience sample of 30 participants (10 per group) will be enrolled to assess feasibility. While we expect it to be very rare, it is possible that some individuals may be determined ineligible after signing consent (because of their baseline MoCA or DASS-21 depression scores). Therefore, we plan to enroll enough patients to obtain data from 30 randomized participants. We estimate that approximately 40 patients may be enrolled to account for dropouts, loss of follow-up, and to achieve this sample size of 30. No a priori power calculation was performed.

Since the primary outcome of the study assesses the overall feasibility of conducting the trial, our descriptive study will record the proportion of patients eligible who meet inclusion without exclusion criteria and decide to participate. The statistics for overall protocol adherence to the intervention will be recorded by reporting the total number of sessions completed out of that required per protocol. We will also assess the total number of questionnaires completed out of the total required.

Descriptive statistics of data will be performed. Categorical data will be reported as proportions and assessed with the use of a chi-square or Fisher’s exact test. Continuous data will be reported as means ± standard deviations or median (quartile 1 and quartile 3) depending on distribution and assessed using analysis of variance (ANOVA). We estimate that with a small sample size it may not be acceptable to assume normality and may be appropriate to use a non-parametric equivalent such as Kruskal–Wallis test when appropriate. A trajectory analysis will be performed to assess changes in the presence of delirium or changes in cognitive function over time. Since the secondary outcomes are exploratory in nature, all tests will be two-sided, with *p* values < 0.05 considered statistically significant. Data will be analyzed using SAS 9.4 (SAS Institute Inc., Cary, NC, USA) or later. Our primary analysis will be conducted using the intention-to-treat principle. All trial reporting will adhere to the Standard Protocol Items: Recommendations for Interventional Trials (SPIRIT; Additional file 1: Table S1).

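### A Severe DASS-21 score drops the participant from the study, not only from meditation; read plainly, a trigger at discharge forfeits that person's one-month and remaining weekly data

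*Protocol article*

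**What the plan says.** All references are to the protocol article.

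- **Removal rule (Adverse event monitoring).** If depression, anxiety or stress on the DASS-21 is in the Severe or Extremely Severe range, "the participant will be dropped out of the study for further clinical evaluation and management". The rule does not distinguish between arms.
- **When DASS-21 is measured (Neurocognitive and psychological assessments).** It is taken at baseline, at discharge ("On the day of discharge, the MoCA, DOW, MOY, CAM, DSI, and the DASS-21 will be completed") and at one month. Discharge is therefore the only scheduled DASS-21 between baseline and one month.
- **What is scheduled after discharge.** For the one-month neurocognitive and psychological assessments: "These will be completed by a blinded research team member via telephone and will include a T-MoCA, DOW, MOY, CAM, DSI, and DASS-21". Under Sleep questionnaires, the PSQI "will be completed at baseline and at the one-month follow-up", and the two PROMIS sleep forms run "weekly after surgery through the one-month follow-up". Meditation, and so the diary, continues to four weeks after surgery in Groups 1 and 2.
- **What is named at withdrawal (Satisfaction survey).** At one month, "or if a participant withdraws from the study, the individuals will be asked to complete a brief satisfaction survey". It covers perceived thinking, memory, attention and wellbeing.
- **Analysis and numbers (Statistical analysis).** "Our primary analysis will be conducted using the intention-to-treat principle". The article also expects that "approximately 40 patients may be enrolled to account for dropouts, loss of follow-up, and to achieve this sample size of 30".

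**The concern.** Referring a severely distressed patient for care is right. The difficulty is that the rule ties this referral to leaving the study. Controls have no meditation to stop, so for them the rule can only remove follow-up.

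Removal depends on the value of an outcome that the trial measures. Those with the worst discharge scores would have no one-month score, so the one-month distress of those who remain looks better than that of everyone randomized. The course after a Severe score, which the article itself treats as a possible adverse event, would go unobserved in exactly the people of interest. The one-month PSQI is the only one after baseline, so these people would have no postoperative PSQI at all.

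The Future direction section says that effect sizes from this trial will inform the endpoints and sample size of the next one. Enrolling about 40 to reach 30 replaces people, but it does not recover the values of those removed.

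**Working it through.** **Plan's own figure.** There is no power calculation to reproduce. The only arithmetic is 30 from about 40, an implied allowance of 1 - 30/40 = 25%. It concerns numbers, not which people are lost.

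**Inputs.** From the article: the removal rule, the assessment schedule, and 10 per arm in three arms. Assumed, because the article does not give them:

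- q, the share of controls Severe or worse at discharge: 2-20%. The low end is plausible because psychiatric history and a baseline depression score above 10 are excluded.
- r, the correlation between discharge and one-month scores: 0.2-0.7.
- Normal scores with SD 1, one score standing in for the three-category trigger, and plain means of those who remain.
- f, the share of the one-month effect already present at discharge: 1, 0.5 or 0.

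**Model.** Discharge score D ~ N(f·δ, 1) and one-month score Y ~ N(δ, 1), with correlation r; lower is better. Y is lost if D > c, where c is the control 1 - q quantile. The mean of Y among those who remain is

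δ - r·φ(c - f·δ)/Φ(c - f·δ).

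**Step 1: control mean (δ = 0).** The shift is -r·φ(c)/(1 - q). For q = 20%, c = 0.842 and φ(c) = 0.280, so φ(c)/(1 - q) = 0.350; at r = 0.7 the shift is -0.245 SD.

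| q | r = 0.2 | r = 0.5 | r = 0.7 |
|---|---|---|---|
| 2% | -0.010 | -0.025 | -0.035 |
| 5% | -0.022 | -0.054 | -0.076 |
| 10% | -0.039 | -0.097 | -0.136 |
| 20% | -0.070 | -0.175 | -0.245 |

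**Step 2: between-arm difference (true δ = -0.50).** At q = 20%, r = 0.7, f = 1, the meditation-arm shift is -0.125, so the difference seen is (-0.500 - 0.125) - (-0.245) = -0.380. The last column is the sample size per arm for the next trial (80% power, two-sided 5%, t-test) if the raw difference is divided by the SD of those who remain. Without loss it is 64.

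| Effect present at discharge | Raw benefit seen, all q and r | Next trial, n per arm |
|---|---|---|
| All (f = 1) | 0.380-0.493 SD | 66-92 |
| Half (f = 0.5) | 0.433-0.496 SD | 65-71 |
| None (f = 0) | 0.500 SD | 51-64 |

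With no true effect, both arms shift equally and the difference stays 0. At middle values (q = 5%, r = 0.5, f = 0.5) the benefit seen is 0.480 SD and n is 67 per arm.

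**Step 3: how often the rule fires.** The count must match the scenario.

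- No effect at discharge: all 30 have rate q, so 0.6 (2%) to 6 (20%) triggers are expected. The chance of at least one is 1 - (1 - q)^30: 45% at 2%, 79% at 5%, 96% at 10%.
- Full 0.50 SD effect at discharge in both meditation arms: their rate is 1 - Φ(c + 0.50), about 0.5% when q = 2% and 9.0% when q = 20%. Expected triggers are 10·q + 20·rate: 0.2 + 0.1 = 0.3 at the low end and 2 + 1.8 = 3.8 at the high end. At 2% the chance of at least one is about 27%.

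**Step 4: against sampling error.** With 10 per arm the standard error of a difference is √(2/10) = 0.447 SD. The largest between-arm shift is 0.500 - 0.380 = 0.120 SD.

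**The case against.** **The article nowhere says that later assessments are not collected.** True. It is a condensed account, and the full protocol may keep such people in follow-up. Contact at withdrawal is also planned, through the satisfaction survey. A reader might infer that the article states an end to all follow-up; it does not. What stands is that leaving the study is the plain meaning of the rule, no section provides otherwise, and the survey does not replace the scales.

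**A reader might infer a contradiction with intention-to-treat.** The text does not support that. The statement names only the primary analysis, and the primary outcome is feasibility, measured by diary adherence. The shifts computed here concern a secondary score. Missing follow-up also does not stop people being analyzed in the arm to which they were randomized. At most, the rule sits awkwardly with that principle.

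**Diary data are the primary outcome, yet no effect on adherence is shown.** Correct. If meditation is stopped on clinical grounds, those sessions would not take place under the fix either. No bias in the adherence estimate is claimed.

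**The size rests on assumptions and its direction is not fixed.** Also correct. With no effect at discharge the raw difference is unbiased, and the next trial's sample size would be too small rather than too large. A full effect by discharge is least plausible in Group 2, which starts meditating only the day after surgery. The model uses means of normal scores, whereas the article expects that nonparametric tests may be needed. For cognition, delirium and sleep the trigger is a different variable, so the shift is probably smaller.

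**The loss would be visible.** Abnormal DASS-21 changes and questionnaire completion are to be reported. That shows how many values are missing, not what they were.

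**Conclusion.** The point holds as a minor design weakness. Read plainly, the rule takes people out of follow-up after randomization on the value of a measured outcome, when clinical safety requires only evaluation and, if needed, stopping meditation. Discharge-day data and everything earlier, including the triggering score, are kept.

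The firmest consequence is descriptive: under the assumed ranges the control one-month DASS-21 mean looks 0.01-0.25 SD too good. The effect on a between-arm difference is modest (0.38-0.50 SD seen for a true 0.50 SD) and depends on how much of the effect is present at discharge. A reader might infer that the next trial will be sized at 92 per arm instead of 64; that is one extreme corner, and other corners give fewer than 64.

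Secondary outcomes are declared hypothesis generating only, and chance variation with 10 per arm exceeds every shift computed. The rule may not fire at all if Severe scores are rare. The primary feasibility conclusion is not shown to be affected.

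**What to change.** Keep the clinical evaluation and management, and pause or stop meditation if clinically needed. In the Adverse event monitoring section, replace the removal from the study with wording such as: the participant is referred for clinical evaluation; meditation may be paused or stopped; with consent, the participant remains in follow-up for all remaining scheduled assessments and is analyzed as randomized. Report the number of Severe or Extremely Severe triggers by arm. Abnormal DASS-21 changes are already to be reported, so only the split by arm is new. If the full protocol already keeps these people in follow-up, one clarifying sentence is enough.

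The cost is one IRB amendment (protocol and consent form) in a trial that is already recruiting. It reaches only participants still in the study or yet to enroll, so two follow-up rules would coexist and the date of change should be recorded. Beyond that it needs only the already scheduled, mostly telephone, assessments for those who trigger: 0.6-6 of 30 under the assumed rates with no effect at discharge, or about 0.3-3.8 with the full effect. The planned sample size does not change.

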### Data collection and management

Data will be collected and stored on REDCap. REDCap is a web-based application that allows for customized data collection and entry [24]. The study team will build and maintain the electronic case report forms on REDCap as well as ensure data completeness and quality periodically by means of internal audits. All efforts will be made to maintain the confidentiality of patient data.

### Statistical analysis

In this feasibility study, a convenience sample of 30 participants (10 per group) will be enrolled to assess feasibility. While we expect it to be very rare, it is possible that some individuals may be determined ineligible after signing consent (because of their baseline MoCA or DASS-21 depression scores). Therefore, we plan to enroll enough patients to obtain data from 30 randomized participants. We estimate that approximately 40 patients may be enrolled to account for dropouts, loss of follow-up, and to achieve this sample size of 30. No a priori power calculation was performed.

Since the primary outcome of the study assesses the overall feasibility of conducting the trial, our descriptive study will record the proportion of patients eligible who meet inclusion without exclusion criteria and decide to participate. The statistics for overall protocol adherence to the intervention will be recorded by reporting the total number of sessions completed out of that required per protocol. We will also assess the total number of questionnaires completed out of the total required.

Descriptive statistics of data will be performed. Categorical data will be reported as proportions and assessed with the use of a chi-square or Fisher’s exact test. Continuous data will be reported as means ± standard deviations or median (quartile 1 and quartile 3) depending on distribution and assessed using analysis of variance (ANOVA). We estimate that with a small sample size it may not be acceptable to assume normality and may be appropriate to use a non-parametric equivalent such as Kruskal–Wallis test when appropriate. A trajectory analysis will be performed to assess changes in the presence of delirium or changes in cognitive function over time. Since the secondary outcomes are exploratory in nature, all tests will be two-sided, with *p* values < 0.05 considered statistically significant. Data will be analyzed using SAS 9.4 (SAS Institute Inc., Cary, NC, USA) or later. Our primary analysis will be conducted using the intention-to-treat principle. All trial reporting will adhere to the Standard Protocol Items: Recommendations for Interventional Trials (SPIRIT; Additional file 1: Table S1).

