### Aims and objectives

We hypothesized that it is feasible to implement a meditation program aimed at improving outcomes in the adult cardiac surgical population. The primary aim of this pilot study is to assess the feasibility of implementing a meditation program in the preoperative period, which will be measured in terms of adherence of the participants to the meditative regimen. Our study will further explore whether a perioperative meditation regimen can result in improvement in postoperative outcomes including pain, sleep, psychological wellbeing, cognitive function, and delirium. Given the pilot nature of the proposed trial, all secondary outcomes will be considered hypothesis generating only.

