### Recruitment and randomization

Individuals will be identified from perioperative surgical consult lists and cardiac surgery clinic visit schedules. If a candidate is eligible for enrollment, he or she will be approached by a member of the research team to discuss the study in detail. Written informed consent will be obtained before initiation of any study procedures.

After obtaining consent, enrolled participants will be randomly assigned to one of three groups using block randomization in a 1:1:1 allocation. REDCap will be utilized to implement the randomization schema while maintaining the blind. REDCap is a secure software designed for rapid data capture tools using metadata table referenced by presentation-level operational modules [24]. Patients will be randomized to one of the following groups:Group 1: Patients are asked to meditate twice daily, starting from least two weeks before surgery, up until four weeks after surgery;Group 2: Patients are asked to meditate twice daily from the day after surgery until four weeks after surgery;Group 3: Patients in the control group will undergo surgery and subsequent hospital stay according to the current standard of care, which does not include meditation.

Patients who are actively meditating previously and are willing to participate in the study will be asked to refrain from meditating during the study period if they are randomized to the control group. They will be required to follow the IK meditation schedule during the period of study participation if they are randomized to one of the intervention groups.

The inclusion of a control group will allow for quantification of the natural history of surgery and postoperative complications. Further, we are utilizing two interventional groups to assess whether a prehabilitative strategy results in differences as compared to a mitigation strategy. Two intervention groups will also help us determine the optimal duration of intervention and the possible impact of duration on compliance and other secondary outcomes.

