### Study outcomes

The primary outcome of the study is to assess the feasibility of implementing a meditation routine in the perioperative period. This will be evaluated using the adherence data from patients’ meditation diary. Secondary exploratory outcomes include effects of the intervention on pain, sleep, psychological wellbeing, cognitive function, and delirium. A number of tools, including pain scores, questionnaires for cognition and delirium assessment, depression and anxiety questionnaire, sleep questionnaires, total opioid consumption and supplemental analgesic requirements in the first 48 h postoperatively, Intensive Care Unit (ICU) stay, and hospital length of stay, will be used to measure the secondary outcomes. In addition, we will also evaluate inflammatory biomarkers measured in plasma. All secondary outcomes will be considered hypothesis generating and interpreted as such (Fig. 2).

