### Meditation adherence

To assess study feasibility, we will evaluate adherence to the study protocol. Patients in the meditation groups will be provided with meditation diaries, where they will be asked to record their daily meditation sessions. Adherence to the meditation schedule will be assessed by calculating the total number of meditation sessions completed divided by the total number of sessions required as per protocol.

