### Ethics and dissemination

This study has been approved by the Committee on Clinical Investigations, Institutional Review Board at Beth Israel Deaconess Medical Center (Protocol 2017-P-000239). Written informed consent will be obtained from all individuals before initiation of study procedures.

Results of the trial will be reported in national and international meetings, as well as in scientific journals. There are no plans to individually notify participants regarding the results of this study. If the feasibility of implementing prehabilitative meditation program in the perioperative period is proven by the study, larger studies can be undertaken to study the effect of meditation in sleep, postoperative pain and cognitive decline.

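### Adherence, the measure named for the primary outcome, rests on 20 planned patients and preoperative adherence on 10, and a single overall session ratio can hide a preoperative failure

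*Protocol article*

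**What the plan says.** All references are to the Protocol article.

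- **Size.** Statistical analysis plans "a convenience sample of 30 participants (10 per group) will be enrolled to assess feasibility". It adds: "We estimate that approximately 40 patients may be enrolled to account for dropouts, loss of follow-up, and to achieve this sample size of 30". It also says plainly: "No a priori power calculation was performed".
- **Primary aim and outcome.** Aims and objectives puts the aim as the "feasibility of implementing a meditation program in the preoperative period", measured by adherence. Study outcomes words the period as perioperative and says of the primary outcome: "This will be evaluated using the adherence data from" the diary that patients keep.
- **Who supplies adherence data.** Meditation adherence: "Patients in the meditation groups will be provided with meditation diaries".
- **Groups.** Patients are "randomly assigned to one of three groups using block randomization in a 1:1:1 allocation". Group 1 meditates twice daily from at least two weeks before surgery to four weeks after it. Group 2 starts the day after surgery and, apart from one practice run at enrolment (Study intervention), does not meditate before it. Group 3 does not meditate.
- **Feasibility statistics.** Statistical analysis lists three: participation among eligible patients, overall adherence as sessions done over sessions due, and questionnaires completed over questionnaires due.
- **Use of the result.** Future direction judges feasibility by reasonable compliance in the intervention groups. Ethics and dissemination looks ahead to larger studies: "If the feasibility of implementing prehabilitative meditation program in the perioperative period is proven by the study".

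**The concern.** The one sample size attached to feasibility is 30, while the measure singled out for the primary outcome cannot be observed in a third of those patients. For the aim as worded in Aims and objectives, it can be observed in only one group. The article does not put a denominator beside each measure, so the reader has to assemble it from several sections.

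The choice of statistic matters more. An overall ratio mixes sessions before and after surgery, and most sessions due fall after surgery. The trial is presented as a test of prehabilitation, and only Group 1 before surgery tests that. If patients practise well after surgery and poorly before it, the overall figure can look good while the preoperative programme has largely failed. The decision on a larger prehabilitation trial would then rest on the wrong number.

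**Working it through.** **1. The plan's own figures.** 3 groups × 10 = 30, as stated. Enrolling 40 to reach 30 implies a loss of 1 − 30/40 = 25%; the article gives no rate. There is no power calculation to reproduce.

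**2. Denominators, by counting the groups that can supply each measure.**

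| Measure | Who supplies it | Planned n |
|---|---|---|
| Participation | all eligible patients | not fixed in advance |
| Questionnaire completion | Groups 1, 2 and 3 | 3 × 10 = 30 |
| Adherence, any period | Groups 1 and 2 | 2 × 10 = 20 |
| Preoperative adherence | Group 1 | 1 × 10 = 10 |

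The Abstract speaks of 40 patients being randomized. On that reading the last two rows become about 27 (80/3) and 13 (40/3), and the pattern is unchanged.

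**3. Share of sessions due before surgery.** Assumptions: a lead-in of exactly 14 days, 28 days after surgery, two sessions a day.

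- Group 1, per patient: 14 × 2 = 28 before and 28 × 2 = 56 after, 84 in all.
- Group 2, per patient: 28 × 2 = 56, all after surgery.
- Both groups: 10 × 84 + 10 × 56 = 1,400 sessions due, of which 10 × 28 = 280 (20%) are preoperative and 1,120 postoperative.

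The 14 days are a minimum. If the lead-in were twice as long and sessions were due throughout, the share would be 560/(560 + 1,120) = 33%, still a minority.

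**4. What the overall ratio can conceal (14-day lead-in).**

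- Half the preoperative and 90% of the postoperative sessions done: (140 + 1,008)/1,400 = 1,148/1,400 = 82%.
- No preoperative session and every postoperative session done: 1,120/1,400 = 80%.

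Computing the ratio per patient does not cure this by itself. In the second case each Group 1 patient scores 56/84 = 67% and each Group 2 patient 100%, a mean of 83% over the 20. The split by period is what reveals the problem.

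**5. Precision.** The article gives neither an expected adherence nor a standard deviation, so both are assumed. The half-width for mean adherence is t(n−1, 0.975) × SD/√n, in percentage points. The interval for a proportion is exact (Clopper–Pearson), with 70% of patients adherent.

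| n | Half-width, SD 20 / 30 / 40 | Exact 95% CI at 70% |
|---|---|---|
| 30 | 7.5 / 11.2 / 14.9 | 21/30: 51–85% |
| 20 | 9.4 / 14.0 / 18.7 | 14/20: 46–88% |
| 10 | 14.3 / 21.5 / 28.6 | 7/10: 35–93% |

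For n = 10 the exact interval is 19–81% at 5/10 and 44–97% at 8/10. The proportions only illustrate scale, because the article defines adherence as a ratio of sessions and sets no cut-off for calling a patient adherent.

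**The case against.** The strongest reply is that nothing stated is false. Statistical analysis places participation and questionnaire completion under feasibility beside adherence, and the controls contribute to both. The sentence giving 30 also gives 10 per group, and the article says that this is a convenience sample without a power calculation. Other sections say openly that diaries are for the meditation groups and that compliance is judged there. All of this stands.

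A reader might infer more than the article supports:

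- *That the sample is overstated 1.5-fold (30/20) or 3-fold (30/10).* The article never says that adherence is measured in 30 patients.
- *That ten patients give an interval running from feasible to not feasible.* No feasibility threshold is stated, so there is no line for the interval to cross.
- *That the lack of a precision calculation is an error.* The article claims no precision, and expected interval widths can properly sit in an analysis plan that is not shown.
- *That the trial announces proof from ten patients.* The sentence in Ethics and dissemination is conditional and announces no result.

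It can also be said that the count of 10 depends on one word. Aims and objectives says preoperative, while the Abstract and Study outcomes say perioperative, which gives 20. That is fair. But the adherence denominator is then still not 30, and the two wordings call for different estimates, so they need to be reconciled. What the reply does not answer is the overall ratio, which would be reported as described and does not isolate the preoperative period.

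**Conclusion.** The point holds as one about denominators and reporting, not as an error of calculation. Adherence can come only from Groups 1 and 2 (planned n = 20), and preoperative adherence only from Group 1 (planned n = 10). These counts follow from the article without any assumption beyond the planned ten per group. Thirty is correct for questionnaire completion.

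Reported overall, adherence would draw only about 20% of its sessions from the preoperative period, given a 14-day lead-in and 28 days after surgery. It could read 82% with half the preoperative sessions missed. That is enough to hide failure of the aim as worded in Aims and objectives. The 20% and the 82% rest on the assumed schedule and completion rates, and the interval widths rest on the assumed adherence and standard deviations.

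**What to change.** In Statistical analysis, give the denominator for each feasibility measure:

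- preoperative adherence: Group 1, planned n = 10;
- postoperative adherence: Groups 1 and 2, planned n = 20;
- questionnaire completion: all 30 randomized;
- participation: all eligible patients.

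Report adherence per patient, by group and by period, with 95% confidence intervals. An overall ratio may be kept beside these but should not stand alone.

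Reconcile preoperative in Aims and objectives with perioperative in the Abstract and Study outcomes. In Ethics and dissemination, replace the language of proof: tie any conclusion on prehabilitation to the Group 1 preoperative estimate and its interval.

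The cost is wording and a few more table rows. No extra patients, visits or data items are needed if the diaries record sessions daily, as Meditation adherence describes. The drawback is that the reported precision will look less favourable than a figure of 30 suggests: at an assumed 70% adherent, 46–88% for 14 of 20 and 35–93% for 7 of 10.
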